#### Timeline of the study

During recruitment, employees will be asked whether they want to participate in the research by one or more health care providers operating in the employability intervention. Participation requires employees to fill in a self-reported online questionnaire at time points T0 (baseline), T1 (6 months after admission), FU1 (12 month follow-up) and FU2 (18 month follow-up). After 18 months the study results for sustainable employability and quality of life are expected to extend into subsequent years. The timeline of the study can also be found in Figure 2.

### Outcome assessment and data collection

The outcome assessment and data collection is identical for every employability intervention. Questions derived from different questionnaires, such as the 'National Working Conditions Survey' (NEA) [18], 'EuroQol 5 Dimensions 5 Levels' (EQ-5D-5 L) [41], 'Short Form Health Survey' (SF-36) [42], 'Trimbos/iMTA questionnaire for costs associated with psychiatric illness' (TIC-P) [43], and 'the productivity and disease questionnaire' (PRODISQ) [44], are combined into a retrospective self-reported questionnaire. The economic evaluation will be analysed from a societal perspective. This means that the most appropriate set of costs captured from the data (e.g. health care costs, productivity costs etc.), regardless of where the costs or benefits occur, will be applied [36].

### Effect evaluation

#### Primary outcome measure

The primary outcome measure in the CASE-study is reduced sickness absence duration in calendar days. Reduced sickness absence will be measured subjectively via patient self-report records. The duration of sick leave will be calculated as the time in calendar days since reduced productivity occurred (baseline). This will then be compared with the productivity time of a person at 6, 12, and 18 months. The success of an intervention will be defined by comparing the average reduction in sickness absence between the intervention group and the control group. The employability intervention is effective when the employees in the intervention group return to work twice as quickly as employees in the control group. Data on sickness absence duration will be gathered by using the productivity and disease questionnaire (PRODISQ) [45].

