#### Participants

Employees eligible for participation in the study will be work-disabled or at risk of work disability due to medical restrictions. In order to identify these employees, we will use employer registration forms, registrations with health care organizations and insurance companies, and registration forms from those providing the intervention. Employees eligible for inclusion will be 18 to 63 years of age, perform paid labour for at least 12 h per week, and are able to communicate in Dutch. Reasons for exclusion are absenteeism for 1.5 years or longer, fulltime students with a student job, informal caregivers and/or volunteers.

In order to recruit a sufficient number of eligible employees, one or more health care providers providing an employability intervention will screen service users for inclusion in the study. When appropriate, information on the research will be provided to the patient. This will be done orally by the health care provider, possibly supported by a handout containing contact information for the researchers, what is expected of participants, privacy concerns, and so on. A self-completion card will be attached to each flyer (handout) consisting of a short checklist for inclusion and informed consent form for signing. The employee is requested to fill in the short checklist, sign the informed consent form, and send these back to the researcher. Participants will have at least 1 week to consider their participation in the study before signing the informed consent form. Participants will be screened for exclusion by the researcher on the basis of answers provided on the checklist. If an employee meets all the selection criteria and is willing to sign the consent form, randomization or matching will then place. Before the intervention starts, the first (baseline) measurement occurs. An email with a login code is sent to all participants, and they will be asked to fill in the baseline questionnaire. The questionnaire for the intervention group is identical to the one for the control group.

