#### Randomization/matching

In the case of randomization, the minimization method will be applied. Minimization aims to ensure an excellent balance for several prognostic factors in small groups [40]. Employees consenting to participate will be pre-stratified according to age (18-32 years, 33-48 years, 49-64 years), gender, and working hours (12-24 h/week, > 24 h/week). Since health care providers will treat participants in both the intervention and in the control groups, the study cannot be blinded. Matching i.e. formulating experimental and control groups on the basis of pairing participants on the basis of predetermined matching criteria will be used. These matched-criteria are age, working hours and health complaints. Thus, an employee in the intervention group will be matched to someone meeting the same criteria who will then act as a member of the control group.

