### Data analyses

#### Effectiveness

All statistical analyses, performed to distinguish differences between the control group and the intervention group, will be performed according to the intention-to-treat principle. This means that the participants will remain in the group they were allocated to at baseline. All data regarding primary and secondary outcomes will be analysed using descriptive statistics. To control for protocol deviations likely to cause bias, data will be analyzed using per-protocol analyses whereby outcomes will be compared between those participants who received at least one or a partial intervention session and the control group. With the aim of correcting for possible regression to the mean, the baseline value of the particular outcome variable will be added to the model. Days of sick leave in the year before the inclusion, measured at baseline, will be added as a potential effect-modifier.

Diagnosis and prognostic parameters can be confounders, thus the Cox regression analysis for confounders will be used to adjust for differences between control and intervention groups. If necessary, differences in baseline will be adjusted for prognostic dissimilarities. Missing data will be handled using SPSS missing value analysis on item level. Completely missing measurements will be handled using multiple imputation.

The primary dependent variable is days of absence from work. In order to estimate the number of absence days, survival analyses will be used. There are two reasons why we opted to use survival statistics. Firstly, the time to sustainable employability is unlikely to be normally distributed which will make parametric statistical analysis difficult or inappropriate. Increasing productivity can occur quite early, possibly within months, but can also, as expected in the care as usual situation, may not be prolonged or may even decrease again. Secondly, survival analysis accounts for dropout by the technique of censoring. Participants who drop out will have the same hazard of sustainable employment than those that remained in the study. The Cox Proportional hazard model will therefore be used to analyse the HR of the days of sick leave duration. Reduced sickness absence duration in calendar days will be analysed with the Kaplan Meier survival method, and the differences in absence duration between both groups will be tested with a log rank test.

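### The primary outcome has an inconsistent time origin: onset of reduced productivity is labelled baseline, although the two dates can lie almost 18 months apart

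*Protocol article*

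**What the plan says.** **Outcome definition.** The protocol article, Primary outcome measure, states: "The duration of sick leave will be calculated as the time in calendar days since reduced productivity occurred (baseline". The same section compares groups at 6, 12 and 18 months and calls an intervention effective when its group returns to work at twice the speed of controls.

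**Baseline elsewhere.** Participants: "Before the intervention starts, the first (baseline) measurement occurs". Timeline of the study lists "time points T0 (baseline), T1 (6 months after admission), FU1 (12 month follow-up) and FU2 (18 month follow-up". In both places baseline is enrolment.

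**Who can enter.** "Employees eligible for participation in the study will be work-disabled or at risk of work disability due to medical restrictions". On prior absence the limit is: "Reasons for exclusion are absenteeism for 1.5 years or longer".

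**Balance on prior absence.** Randomization/matching says of the quasi-experiments: "These matched-criteria are age, working hours and health complaints". For the randomised evaluations, "Employees consenting to participate will be pre-stratified according to age", with gender and working hours as the other factors. Neither list includes prior absence.

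**Analysis.** Effectiveness plans Kaplan-Meier curves, a log-rank test and a Cox model. It says that "the baseline value of the particular outcome variable will be added to the model" and that sick-leave days in the year before inclusion will be added as a potential effect-modifier. Delayed entry is not mentioned.

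**The concern.** Onset of reduced productivity and T0 are the same date only for someone whose productivity falls on the day of enrolment. Anyone already absent at entry has two candidate start dates, and the sentence names both.

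The choice matters for three reasons.

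- On the onset clock, each participant brings a stretch of absence that was over before enrolment. No return could have been observed in it, because people who returned earlier were not recruited. An ordinary survival analysis nevertheless counts it as time at risk.
- In a balanced comparison, pre-study days that vary between people blur the contrast and pull the HR towards 1. Any ratio of durations shrinks as well, and that bears on the success rule.
- In a matched comparison, a group difference in prior absence can look like a treatment effect.

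The onset clock also has no clear start for entrants who are only at risk. Nor is reduced productivity the same as sick leave: the Background separates working while ill from being absent.

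**Working it through.** **1. The plan's own figures.** Sample size gives HR 2.0, 80% power, 0.05 significance, 120 employees and 15% dropout. 120 / 0.85 = 141.2, so 142, as stated. Two-sided, the Schoenfeld formula needs 4 × (1.960 + 0.842)² / (ln 2)² = 65.3, so 66 events. 66 / 120 = 55% of participants returning. With exponential times and HR 2.0, if a share S of controls has not returned by 18 months, the intervention share is S². Solving [(1 − S) + (1 − S²)] / 2 = 0.55 gives S = 0.572, so about 43% of controls return. The plan does not state this return rate. It is the rate that makes 120 consistent with the other inputs.

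**2. Gap between the two dates.** Prior absence may be anything under 1.5 years: 1.5 × 365.25 = about 548 days. A prior-year variable can cover at most 365 of them.

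**3. Balanced arms, true HR 2.0.** Assumptions not in the documents: exponential time to return after T0, 1:1 allocation, 548 days of follow-up, and prior absence uniform on 0-548 days in both arms unless stated. HRs are from large simulated samples; power is for 120 analysed.

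| Controls returning by 18 months | HR, T0 clock | HR, onset clock | HR, onset with delayed entry | Power, T0 → onset |
|---|---|---|---|---|
| 43% | 2.00 | 1.94 | 2.00 | 80% → 76% |
| 70% | 1.98 | 1.84 | 1.98 | 91% → 85% |
| 90% | 2.00 | 1.70 | 2.00 | 95% → 79% |

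Separate runs gave up to 1.97 at the low return rate. With a control median of 3 months the onset-clock HR was about 1.5; there the return by 18 months is 1 − 2^(−18/3) = 98%. If half the entrants have no prior absence, the three onset-clock HRs are 1.92, 1.79 and 1.62. If prior absence is at most 180 days, they are 1.96-1.98. If everyone has exactly 180 days, the HR does not change.

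**4. Ratio of durations.** With 70% of controls returning, post-T0 medians are 315.5 and 157.7 days, a ratio of 2.0. Adding 180 pre-study days to both arms gives (315.5 + 180) / (157.7 + 180) = 495.5 / 337.7 = 1.47.

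**5. Unequal prior absence, true HR 1.0, no adjustment.** Control return is 43-70% in the first two rows.

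| Excess in controls | HR, onset clock | Rejection at 5% | HR, T0 clock |
|---|---|---|---|
| 60 days | 1.14-1.18 | 6-11% | 1.0 |
| 90 days | 1.23-1.28 | 12-20% | 1.0 |
| Means of 6 v 3 months (uniform 0-12 v 0-6), control medians 3-12 months | 1.3-1.8 | not computed | 1.0 |

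**6. With prior-year sick-leave days as a Cox covariate on the onset clock.** In the last case of step 5 the HR falls from 1.79 to 0.97 (median 3 months) and from 1.49 to 1.04 (median 6 months). With 60 extra control days it falls from 1.15-1.16 to 1.01-1.04 at 43-70% control return. For a true HR of 2.0 in balanced arms it gives 2.02-2.20, a mild overcorrection.

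**The case against.** The strongest reply is that the article means T0. The sentence contains the word baseline, two other sections define baseline as enrolment, and the 6-, 12- and 18-month comparisons follow the T0 schedule. On that reading no pre-study day enters the outcome. This stands. A reader might infer that the planned analysis is biased, but the documents support only that its time origin is contradictory.

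Second, Effectiveness already plans to bring in prior-year sick leave and to adjust the Cox model for baseline differences. This largely stands for imbalance, as step 6 shows. It does not reach the log-rank test as described, and it leaves out absence more than a year old. The variable is also called an effect-modifier, so its use as a plain covariate is an assumption.

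Third, the largest distortions need high return rates and wide prior absence. This stands too. At the return rate implied by 120 participants, a balanced comparison loses little, and no document gives the size of any imbalance.

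A reader might also infer that on a T0 clock the planned baseline adjustment is empty throughout. That is so only for the primary outcome, where duration at T0 is zero for everyone. Health status and quality of life have real baseline values.

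Finally, a condensed article need not spell out delayed entry. Its absence is no fault in itself. The fault is that the article does state an origin, and the statement conflicts with its other sections.

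**Conclusion.** The point holds as a contradiction in the definition of the primary outcome. The article counts from onset of reduced productivity, calls that date baseline, uses baseline for T0 elsewhere, and admits people with just under 1.5 years of absence.

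The harm depends on the literal reading without delayed entry:

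- **Balanced arms.** A true HR of 2.0 becomes about 1.9-1.97 at 43% control return and about 1.5-1.7 at roughly 90% or more, given prior absence uniform on 0-18 months. It hardly changes if prior absence is short or equal for all.
- **Matched designs.** With no true effect, the unadjusted HR is about 1.14-1.28 for 60-90 extra control days at 43-70% control return. It reaches 1.3-1.8 for a three-month mean difference with wide spread. The prior-year variable removes most of this in the Cox model if entered as a covariate.

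The exponential return times, the return rates and the prior-absence distributions are assumptions. On the T0 reading none of this arises, but the words about reduced productivity are then wrong and need correcting.

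**What to change.** In Primary outcome measure, set time zero at T0 (the allocation or matching date) in both groups and count only calendar days of absence after T0. State how entrants who are not absent at T0 are counted. Record the first day of the current absence spell in the T0 questionnaire, and enter days already absent at T0 as a covariate in the Cox model. If the onset scale is kept instead, use delayed entry at T0 in the Kaplan-Meier, log-rank and Cox analyses.

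The cost is a changed sentence in the definition and one date item in the questionnaire. The downside of the T0 clock is that reported durations no longer describe the whole sickness spell.

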**Methods/design:**

Per employability intervention 142 participants are needed whereof approximately 66 participants receiving the intervention will be compared with 66 participants receiving usual care. Based on the intervention-specific characteristics, a randomized control trial or a quasi-experiment with match-criteria will be conducted. Notwithstanding the study design, eligible participants will be employees aged 18 to 63, working at least 12 h per week, and at risk of work disability, or already work-disabled due to medical restrictions. The primary outcome will be the duration of sick leave. Secondary outcomes are health status and quality of life. Outcomes will be assessed at baseline and then 6, 12 and 18 months later. Economic costs will consist of healthcare costs and cost of lost production due to work disability, and will be evaluated from a societal perspective.

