
### Sample size

For the economic evaluation of the three newly developed employability interventions, the study sample size was pre-specified by the researchers and the developers of the particular interventions. For the sample size calculation of the existing 'Best Practices', we expect that a Hazard Ratio (HR) of 2.0 indicates a relevant difference in the average number of hours/days of lost work due to work disability between employees in the intervention group and employees in the control group after 18 months. This HR is based on findings of recent studies in occupational health care [25,52-55]. With a power of 80% at a 0.05 significance level, the sample size was calculated to be 120 employees [56]. Taking into account a dropout rate of 15%, 5% per follow-up measurement time, a total of 142 participants are needed. A dropout is defined as an employee who has not filled in the questionnaire at one or more measurement time-points.

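### The success rule puts its pass mark at the planning effect (a factor of two, HR 2.0), so the stated 80% power does not apply to it: read on the point estimate, it is met about half the time when the true HR is 2.0

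*Protocol article*

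**What the plan says.** All references are to the protocol article.

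- **Primary outcome measure** gives a decision sentence: "The employability intervention is effective when the employees in the intervention group return to work twice as quickly as employees in the control group". It names no estimate, confidence limit or test. The preceding sentences include a more general one: "The success of an intervention will be defined by comparing the average reduction in sickness absence between the intervention group and the control group". That one sets no threshold.
- **Sample size**, for the two 'Best Practices' only, takes it that "a Hazard Ratio (HR) of 2.0 indicates a relevant difference in the average number of hours/days of lost work due to work disability" and continues: "With a power of 80% at a 0.05 significance level, the sample size was calculated to be 120 employees". Allowance for dropout follows: "Taking into account a dropout rate of 15%, 5% per follow-up measurement time, a total of 142 participants are needed". The sizes for the three newly developed interventions were set separately.
- **Data analyses, Effectiveness** estimates an HR with a Cox model and says that "the differences in absence duration between both groups will be tested with a log rank test".

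No section says how the doubling criterion relates to the log-rank test, or which of the two decides.

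**The concern.** A trial sized to detect an effect has its stated power for rejecting no effect when the planning value is true. It does not have that power for observing an effect at least as large as the planning value. Here the pass mark in the decision sentence and the planning effect are the same factor of two, so a reader who takes both sections at face value would think the rule has an 80% chance of being met when the assumption is right.

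At stake is the effectiveness conclusion. An intervention that shortens absence with a clearly significant result could be reported as not effective. Because the article does not say which criterion governs, the choice could also be made after the data are seen. The Discussion says that the design will be applied to each intervention in the project, so the ambiguity would recur in each report.

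**Working it through.** **Inputs from the article.** HR 2.0, power 80%, significance level 0.05, 120 employees before dropout, 15% dropout, 142 in total (all Sample size); roughly equal groups ("approximately 66 participants receiving the intervention will be compared with 66 participants receiving usual care", abstract).

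**Inputs not stated, assumed here.** Two-sided testing, and the number of return-to-work events d. An HR above 1 means faster return to work.

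**Step 1: the plan's own figures.**
- Schoenfeld: d = 4(1.960 + 0.842)² / (ln 2)² = 4 × 7.85 / 0.480 = 65.4, so 66 events.
- Freedman: d = (1.960 + 0.842)² × [(2 + 1)/(2 − 1)]² = 7.85 × 9 = 70.6, so 71 events.
- For 120 employees to yield these, 66/120 = 55% or 71/120 = 59% must return to work. The article gives no such proportion, so 120 is plausible but cannot be reproduced from stated inputs.
- Dropout: 120 / (1 − 0.15) = 141.2, rounded up to 142, as stated.

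The 66 events are back-calculated. They are not the 66 participants per group in the abstract.

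**Step 2: chance of meeting the rule on the point estimate.** With equal groups, the estimated log HR is approximately normal with mean equal to the true log HR and SE = 2/√d. At a true HR of 2.0:

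P(observed HR ≥ 2.0) = 1 − Φ[(ln 2 − ln 2)/SE] = 1 − Φ(0) = 50%.

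SE cancels, so the result does not depend on d, and a larger sample does not raise it.

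**Step 3: comparison with the log-rank test.** The smallest significant observed HR is exp(1.96 × SE). Power at HR 2.0 is Φ(ln 2/SE − 1.96).

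| Events d | SE | Smallest significant HR | Significant at true HR 2.0 | Observed HR ≥ 2.0 | Significant but below 2.0 |
|---|---|---|---|---|---|
| 66 | 0.246 | 1.62 | 80.4% | 50% | 30% |
| 71 | 0.237 | 1.59 | 83.2% | 50% | 33% |
| 120 (all return) | 0.183 | 1.43 | 96.7% | 50% | 47% |

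In every row an observed HR of 2.0 or more is already significant, so requiring significance as well leaves the 50% unchanged.

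**Step 4: other true effects, with 66 events.** P(observed HR ≥ 2.0) is 12% at a true HR of 1.5, 33% at 1.8, 65% at 2.2 and 82% at 2.5. An 80% chance needs a true HR of exp(ln 2 + 0.842 × 0.246) = 2.46.

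**Step 5: other readings of the rule.**
- Lower 95% limit above 2.0: the chance at a true HR of 2.0 is 1 − Φ(1.96) = 2.5%. With 66 events the observed HR would have to exceed 2 × 1.62 = 3.24.
- Ratio of medians or means: simulated with 60 per group, exponential times, censoring at 18 months and 4000 runs per scenario. The Cox HR reached 2.0 in 49.9% to 51.0% of runs. A ratio of medians of at least 2 occurred in 49% to 51% when the control median fell within 18 months. In the slowest scenario it was 76%, where the true control median is beyond 18 months and a control median that was not reached was counted as meeting the rule. A ratio of mean durations truncated at 18 months reached 2 in 0% to 44%, depending on the assumed return rate.

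**The case against.** The best defence is that the sentence is not a decision rule. It puts the target effect in plain words, the Sample size section powers for that effect, and the Effectiveness section tests it. On that reading the log-rank test decides and the 80% stands. The sentence mentions no observed value, hazard ratio or confidence limit, so the reading is open. But the article never says it. The wording is that of a verdict, whereas the Sample size section uses different language for a relevant difference. The Objectives hypothesise only that the intervention is preferable to usual care. The defence shows that the sentence is ambiguous; it does not remove the problem.

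Other objections stand and limit the point:

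- The article attaches 80% only to the sample size calculation and never claims it for the doubling rule.
- The event count and sidedness are assumptions. Of the point-estimate results at a true HR of 2.0, only the 50% is free of the event count; 1.62 and 30% are not.
- A doubling of speed equals HR 2.0 exactly only under exponential times.
- A relevance threshold stricter than significance can be a legitimate choice, provided its operating characteristics are stated.

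**Conclusion.** The point holds as a mismatch between the stated pass mark and the powered test. Applied to the point estimate, with a doubling read as HR 2.0, the rule is met about 50% of the time at a true HR of 2.0, for any number of events. Applied to the lower 95% limit, it is met about 2.5% of the time. With two-sided testing, the share of trials that would be significant yet labelled not effective is about 30% with 66 events and 47% with 120. The contrast with 80% applies to the two 'Best Practices', the only interventions for which that calculation is given.

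Three stronger inferences are tempting but unsupported:

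- **That the 80% is miscalculated.** It is consistent with a log-rank test at HR 2.0 if 55% to 59% return to work; it simply belongs to that test.
- **That the cost-effectiveness results depend on the effectiveness verdict.** The Economic evaluation part of the analysis section computes the cost-effectiveness and cost-utility ratios, bootstrap uncertainty and acceptability curves with no condition that the intervention was found effective.
- **That there are three competing pass marks.** The sentence on average reduction names a comparison without a threshold, and the log-rank test is the method of analysis. Only the doubling sentence sets a pass mark.

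**What to change.** Replace the decision sentence under Primary outcome measure with one rule: effectiveness is judged by the pre-specified return-to-work HR (log-rank test and Cox model), and is concluded if its 95% confidence interval excludes 1 in favour of the intervention. Keep HR 2.0 as the planning value and report the estimate and its interval against it.

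If the doubling threshold is kept, say that it applies to the point estimate and that its chance of being met at a true HR of 2.0 is about 50%, not 80%.

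Either change costs a sentence or two of text. Neither needs more participants or data.
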